### Eligibility and recruitment

2.3

Participants will be recruited from colleges in Changchun, in the Jilin Province in China. Students will be recruited through live lecture, poster promotion and official account by researchers and staff. Eligible subjects will be screened through a combination of face-to-face surveys and a QR code through the We-Chat Star questionnaire. Inclusion criteria for participants will be: (1) college students aged 18 years or older; (2) individuals meeting the diagnostic criteria for StD (they will not meet the diagnostic criteria for MDD according to the Diagnostic and Statistical Manual of Mental Disorders (DSM-V) (33) and their Center for Epidemiologic Studies Depression Scale (CES-D) score will be 16 or higher); (3) individuals who have not received depression treatment in the past 6 months and have no plans to receive treatment outside of this study; and (4) individuals who have volunteered and agreed to participate in the study and signed informed consent. Participants will be excluded if: (1) they present an intellectual disability and/or physical limitations (such as severe mobility, visual or hearing impairments, history of asthma, heart disease, etc.); (2) they have prior experience using the Nintendo Switch (to ensure consistency or comparability in gaming experience among the participants); (3) they present other types of mental disorders (to ensure research focus, accuracy, safety, and ethical compliance); and (4) they present a suicide risk (to ensure safety and ethical compliance of participants).

### Randomization, allocation and blinding

2.4

Participants will be randomly allocated to the intervention or control groups in a 1:1 ratio using computer-based permuted block randomization. The randomization sequence will be generated by an independent research coordinator, and the details of group allocation will be concealed on cards placed inside sequentially numbered, sealed opaque envelopes. Outcome evaluators, data analysts and study coordinators will be kept blinded.

### Interventions

2.5

#### Pre-experiment

2.5.1

Before the pre-experiment, participants will be involved in two exergame practice sessions, lasting 60 min each. The pre-experiment will be conducted using a 2-week exergame program (test version; Supplementary Table S1), including 2–3 sessions per week (34), lasting 50–60 min each. During the first week of the exergame program, participants’ heart rates will be monitored using smart sports bracelets, and their maximum heart rate (HRmax) will be estimated using the formula HRmax = 207–0.7 × age to inform subsequent exercise intensity. The Physical Activity Rating Scale-3 (PARS-3) will be used to understand participants’ athletic abilities and preferences for the type of exercise. Additionally, the Favorite Exergame Questionnaire (FEQ) developed by our team and based on the “Fitness Ring Adventure” game, will be used to assess participants’ levels of interest, satisfaction, and enjoyment for the exergames (see Supplementary Table S2). Following this, a Nintendo Switch-based exergame combination program (preliminary version) will be set up, including “Warm-up,” “Exergame” and “Cool-down” phases. The program will be designed based on the information gathered and the exergame menu (see Supplementary Table S3).

The second week will be devoted to establishing the game plan (preliminary version), with the same intervention duration and frequency as in the first week. The intervention program will be adjusted according to the participants’ feedback and the recommendations of psychiatric nursing experts and sports training experts. For example, the content of the exercise game should progress from easy to difficult, be adjusted according to the participant’s interest, satisfaction, and enjoyment, and be diversified to include more game content, to increase interest and motivation for participation. The above information will result in a final Nintendo Switch-based exergame combination program (see Table 1 for an example of Week 1 and Supplementary Table S4 for the remaining 7 weeks).

**Table 1 tab1:** The Nintendo Switch-based exergame combination program.

Intervention time		Intervention content		Duration
Week 1	Warm-up		Dynamic Stretch Arm stretch (raise both arms and push forward) Abdominal stretch (swing arms, raise both arms and lean sideways) Leg stretch (step, deep squat) Yoga stretch (twisting seated pose)	5.5 min
	Exergame	Match1^a^	Adventure mode	30–40 min
		Match2^b^	Chest muscle training, Whack-a-mole Parachuting Squat jumps Icino land	10 min
	Cool-down		Stretching exercises^c^	4.5 min

^a^After each workout, keep a record, and finally accumulate and record the total score. ^b^Choose 1–2 challenges provided for completion. ^c^Stretching exercises focus on relaxing the abdominal, lumbar, and leg areas. mins, minutes.

#### Formal intervention

2.5.2

##### Intervention group

2.5.2.1

Before the intervention, two practice sessions will be conducted, lasting 60 min each. In the first session, a trained researcher will explain and demonstrate how to operate the equipment and will guide the participants through the exercises to familiarize them with the operation process and methods. In the second session, two researchers will assess participants’ proficiency in using the system and provide individualized guidance to ensure that all participants fully understand the system’s operation process and methods. In addition, at the end of the session, participants will receive a video recorded by the researcher demonstrating the operation procedures and methods, allowing those who may need additional time to familiarize themselves with the system.

The intervention group will be involved in the study for a total of 16 weeks, consisting of an 8-week intervention period and an 8-week follow-up period. The EIG will take part in the Nintendo Switch-based exergame combination program in an appointed psychological laboratory. Researchers will conduct the one-on-one intervention for 8 weeks, with 2–3 sessions per week, lasting 50–60 min each. Each session will include three phases: “Warm-up,” “Exergame” and “Cool-down” (see Supplementary Table S5, Figure S1 for details). To ensure game compliance and increase participation, the content of the program design will be different every week. The content of the “Cool-down” phase will be adjusted every 2 weeks, and the content of the exergame “Match 2” will be adjusted every week, and its difficulty and intensity will be increased gradually. Every Sunday, the week’s “Match 1” and “Match 2” results will be announced, and the following week’s game content will be released.

During the intervention, the researchers will keep an eye on the participants’ state to ensure the daily safety of the students.

##### Control group

2.5.2.2

Participants in the control group will maintain their original lifestyle and will not receive any other intervention.

### Outcome measures

2.6

#### Quantitative outcome measures

2.6.1

Students both in the intervention and the control groups will be assessed on their levels of depressive and anxiety symptoms, sleep quality, participation adherence, and quality of life at T0, T1, T2 and T3. See Table 2 and Supplementary Figure S2 for a detailed description of data collection.

**Table 2 tab2:** Overview of data collection.

Measures	T0	T1	T2	T3
Demographics	△			
CES-D	△	△	△	△
PHQ-9	△	△	△	△
GAD-7	△	△	△	△
PSQI	△	△	△	△
SF-12	△	△	△	△

T_0_, pre-intervention (week 0); T_1_, post-intervention (week 8); T_2_, 1-month follow-up (week 12); T_3_, 2-month follow-up (week 16); CES-D, Center for Epidemiologic Studies Depression Scale; PHQ-9, Patient Health Questionnaire-9; GAD-7, Generalized Anxiety Disorder-7; PSQI, Pittsburgh Sleep Quality Index; SF-12, 12-Item Short Form Health Survey.

##### The center for epidemiologic studies depression scale

2.6.1.1

Depressive symptoms will be measured using the Center for Epidemiologic Studies Depression Scale (CES-D), developed by Radloff et al. and revised by Zhang et al. (35, 36). It consists of 20 items using a 4-point Likert scale, ranging from “rarely or none of the time (less than 1 day)” to “most or all of the time (3–4 days).” The total score ranges between 0 and 60, with higher scores indicating greater levels of depression. A Cronbach’s α coefficient of 0.90 has been reported (35).

##### The patient health questionnaire-9

2.6.1.2

The PHQ-9 (37) contains nine items, including loss of pleasure, low mood, sleep difficulties, lack of energy, eating disorders, low self-esteem, concentration difficulties, slow movement, and self-harm/suicidal ideas. These items use a 4-point Likert scale, ranging from “not at all” to “nearly every day.” The total score ranges from 0 to 7, with a higher score indicating a higher severity. This scale had a satisfactory Cronbach’s α coefficient among students (38, 39) and the internal consistency of the scale was also good.

##### The generalized anxiety disorder scale

2.6.1.3

Anxiety symptom severity will be measured using the GAD-7, which consists of 7 items using a 4-point Likert scale, ranging from “Not at all” to “Nearly every day.” The total score ranges from 0 to 21, and scores of 5, 10, and 15 represent cut-points for mild, moderate, and severe anxiety, respectively. The scale has a Cronbach’s alpha coefficient of 0.92 and a retest reliability coefficient of 0.83 (40).

##### The Pittsburgh sleep quality index

2.6.1.4

Sleep quality will be measured using the PSQI (41), which consists of seven subcategories: subjective sleep quality, use of sleeping medication, sleep latency, sleep disturbances, sleep duration, daytime dysfunction, and habitual sleep efficiency. The questionnaire consists of open-ended questions and 4-point Likert items, ranging from “Not during the past month” (0) to “Three or more times a week” (3) or from “Very good” (0) to “Very bad” (3), with higher scores indicating worse sleep quality. Lu et al. (42) reported a test–retest reliability of 0.994, a split-half reliability coefficient of 0.824, and an overall Cronbach’s alpha coefficient of 0.845 for the PSQI. In addition, the structural validity of the PSQI was 0.76, and the categorical validity was 0.81, indicating good reliability and validity (42).

##### The 12-item short form health survey

2.6.1.5

The SF-12 (43) consists of 12 items measuring 8 health domains. It can be divided into a Physical Component Summary (PCS) and a Mental Component Summary (MCS). PCS includes Physical Functioning (PF), Role Physical (RP), Bodily Pain (BP), and General Health (GH) items. MCS includes Vitality (VT), Social Functioning (SF), Role Emotional (RE), and Mental Health (MH) items. The total score ranges from 0 to 100, with higher scores indicating better physical and mental health functioning. A score of 50 or higher is considered within the normal range.

##### Adherence

2.6.1.6

The intervention was deemed successful if participants achieved at least 80% of the total target practice time (24). Based on an intervention design of 2–3 sessions per week for a period of 8 weeks, with each session lasting 50–60 min, the target practice time per week ranges from 100 (50 min × 2 times) to 180 (60 min × 3 times) minutes, the average target practice time per week is 140 min ((100 min + 180 min)/2), and the total target practice time is 1,120 min (140 min/week × 8 weeks). 80% of the total target practice time corresponds to 896 min (1,120 min × 80%). During the 8-week intervention, if the actual practice time of each participant reaches or exceeds 896 min, the completion standard is met.

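### The single 896-minute adherence cut-off does not fit the permitted schedule: full attendance at the protocol's own lower target gives 800 minutes and fails, while about 62–75% attendance on a three-session schedule passes

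*Protocol article*

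**What the plan says.** Section 2.5.2.1 (Intervention group) sets the programme: "Researchers will conduct the one-on-one intervention for 8 weeks, with 2–3 sessions per week, lasting 50–60 min each". Section 2.6.1.6 (Adherence) starts from the same range and states that "the target practice time per week ranges from 100 (50 min × 2 times) to 180 (60 min × 3 times) minutes". It averages those two extremes to 140 minutes per week, multiplies by 8 weeks to reach 1,120 minutes, and takes 80% of that. The criterion is introduced as a proportion: "The intervention was deemed successful if participants achieved at least 80% of the total target practice time". It is then applied to individuals as an absolute number of minutes: "if the actual practice time of each participant reaches or exceeds 896 min, the completion standard is met".

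Nothing in the document assigns participants to two or to three sessions, ties the cut-off to a participant's own schedule, or makes an exception for the lower end of the range.

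Section 2.6.1 (Quantitative outcome measures) describes both arms as being "assessed on their levels of depressive and anxiety symptoms, sleep quality, participation adherence, and quality of life at T0, T1, T2 and T3".

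**The concern.** A criterion described as 80% of target should be reachable by someone who attends everything the protocol asks, and should not be met by someone well short of 80%. When the target is a range and the cut-off is 80% of its midpoint, neither is guaranteed. The total of 1,120 minutes is 1.4 times the lower permitted total (800) and about 0.78 of the upper one (1,440), so the share of sessions needed to pass depends on which permitted schedule a participant followed.

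Adherence is a listed quantitative outcome, and Section 2.6.1.6 links this cut-off to whether the intervention is judged a success. The Discussion names sustained engagement as a main challenge, and the Conclusion expects the intervention, if effective, to be easy to adhere to. The 896-minute rule is the only adherence measure the document defines, so any reported adherence rate rests on it.

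**Working it through.** **Inputs.** Sessions per week: 2–3. Minutes per session: 50–60. Duration: 8 weeks (Sections 2.5.2.1 and 2.6.1.6). Adherence proportion: 80% (Section 2.6.1.6).

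**Reproducing the plan's figure.** (2 × 50 + 3 × 60)/2 = (100 + 180)/2 = 140 min/week. 140 × 8 = 1,120 min. 0.80 × 1,120 = 896 min. This agrees with the protocol.

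**Full attendance against the cut-off.** Full-attendance minutes = sessions per week × minutes per session × 8. Share needed = 896 / full-attendance minutes. Sessions needed = 896 / minutes per session, rounded up.

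| Schedule | Full attendance (min) | Share needed | Sessions needed | 80% of own schedule (min) |
|---|---|---|---|---|
| 2 × 50 | 800 | 112.0% | 18 of 16 (impossible) | 640 |
| 2 × 55 | 880 | 101.8% | 17 of 16 (impossible) | 704 |
| 2 × 60 | 960 | 93.3% | 15 of 16 | 768 |
| 2 and 3 alternating, 55 | 1,100 | 81.5% | 17 of 20 | 880 |
| 2 and 3 alternating, 56 | 1,120 | 80.0% | 16 of 20 | 896 |
| 3 × 50 | 1,200 | 74.7% | 18 of 24 | 960 |
| 3 × 55 | 1,320 | 67.9% | 17 of 24 | 1,056 |
| 3 × 60 | 1,440 | 62.2% | 15 of 24 | 1,152 |

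**Break-even at two sessions per week.** 896 / 16 = 56 min. A constant two-session schedule averaging less than this cannot pass at 100% attendance. At 2 × 50 the shortfall is 896 − 800 = 96 min.

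**The other direction.** At 3 × 60, 15 of 24 sessions give 900 min and pass at 62.5% attendance. At 3 × 50, 18 of 24 sessions also give 900 min and pass at 75%. Both are below the stated 80%.

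**Is a 50-minute session a shortened one?** No. The phases in Table 1 sum to 5.5 + 30 + 10 + 4.5 = 50 min at the short end and 5.5 + 40 + 10 + 4.5 = 60 min at the long end. A 50-minute session contains every phase.

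**Do the two 60-minute practice sessions close the gap?** Adding 120 min to 800 would give 920 and a pass. But Section 2.5.2.1 places them before the intervention, and Section 2.6.1.6 counts time during the 8 weeks.

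**Adherence as a both-arm outcome.** Section 2.6.1 lists it for both groups at all four time points. Section 2.5.2.2 gives controls no intervention, so they have no practice time. Section 2.6.1.6 confines adherence to the 8-week intervention, so it has no value at T0 and no new value at T2 or T3. Table 2 has no adherence row.

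**The case against.** The best defence is that a single minimum exposure is a legitimate choice. The protocol also calls the cut-off a completion standard on actual practice time, and someone who received 900 minutes has had more exercise than a full attender at 2 × 55. That would justify an absolute minimum described as exposure. It does not justify one described as 80% of target when the protocol's own lower target, fully met, falls below it.

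Several other points on this side stand and limit the finding:

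- A reader might infer a calculation error. There is none; every step to 896 reproduces. Taking the midpoint of the weekly extremes is openly stated.
- A reader might infer that nobody faces an 80% standard. The weekly range also allows a mix of two- and three-session weeks, and 20 sessions of 56 minutes face exactly 80%. The constant schedules in the table are illustrations, not groups that the protocol defines.
- A reader might infer that the rule captures schedule and not attendance. It captures both: a three-session participant who misses enough sessions still fails, and full attendance at 2 × 60 or on any three-session schedule passes.
- A reader might infer harm to the efficacy analysis or to a completer analysis. Section 2.8 plans no completer, per-protocol or dose–response analysis, and neither the sample size nor the group × time model uses 896.
- A reader might infer that full attenders on the lower schedule would be barred from interview, because Sections 2.2 and 2.6.2 select those who completed the 8 weeks. Neither section refers to the cut-off, so this is not established.

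The both-arm wording in Section 2.6.1 is a loose summary sentence that Table 2 already contradicts. It is a small correction and adds no weight to the point about the cut-off.

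**Conclusion.** The point holds as an inconsistency between the cut-off and the permitted schedule. Followed exactly, the rule fails a participant with 100% attendance at two sessions per week averaging under 56 minutes, and passes one with about 62–75% attendance on a constant three-session schedule. The share of scheduled time needed runs from 112% at the floor of the permitted range to 62% at its ceiling, and is near 80% only around the midpoint.

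The table assumes a constant schedule over 8 weeks except where alternation is shown, and a constant session length. The document does not give the distribution of sessions per week or of session length, so neither the number misclassified nor the net direction of error in the adherence rate can be computed. The consequence is confined to the adherence outcome and what is concluded from it.

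**What to change.** Reconcile Sections 2.5.2.1 and 2.6.1.6 without altering the intervention schedule. Keep the 80% rule and apply it to each intervention-group participant's own denominator: sessions (or minutes) attended over weeks 1–8, divided by sessions (or minutes) scheduled for or offered to that participant, with adherence met at 0.80 or more. State which unit is used. If sessions are used, the requirement is 13 of 16 (0.8 × 16 = 12.8), 16 of 20, or 20 of 24 (0.8 × 24 = 19.2). The denominator should be set before the sessions take place; otherwise a missed third session could be recorded as a two-session week. Report total minutes separately, as exposure.

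In Section 2.6.1, take adherence out of the list of outcomes assessed in both arms at T0–T3, and define it for the intervention group over the 8 weeks.

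The cost is small but more than wording. The document describes neither individual schedules nor an attendance log; the only per-session record it mentions is the Match 1 record in the Table 1 footnote. Scheduled and attended sessions (with durations, if minutes are used) must therefore be recorded for each participant. The reported adherence rate may change, so the definition should be settled before adherence results are seen.

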#### Qualitative data collection

2.6.2

The college students with StD who have completed the 8-week Nintendo Switch-based exergame intervention will be invited to participate in one-on-one, face-to-face semi-structured interviews to explore their experiences of taking part in the intervention. Table 3 shows the details of the interview outline.

**Table 3 tab3:** Semi-structured interview outline.

Number	Questions
1	What was your initial reason (or motivation) for participating in the exergame intervention? Please describe your reasons in order of importance.
2	What are your feelings after attending the exergame intervention?
3	What challenges have you encountered when participating in the exergame intervention? What was the biggest challenge? How was it resolved? Please provide examples and details.
4	Would you like to participate in other activities similar to the exergame intervention in the future? Would you recommend the exergame intervention to other people? Please state specific reasons.
5	What traditional exercise activities have you participated in before? In what ways do you think this combination of exercise and play could benefit you more than traditional exercise methods?
6	What kind of support and assistance in the exergame intervention would you like to receive in the future? Please be specific about what you think needs to be improved and refined.
7	Is there anything else you would like to add to today’s conversation?

### Quality control

2.7

Our team is an experienced group of researchers, consisting of two senior experts in the fields of mental health and nursing and three graduate students specializing in nursing. If there are complex clinical issues, the researchers in our team and professional experts in the field of clinical psychiatry will work together to find solutions.

The researchers will provide uniform and standardized training to all the personnel responsible for implementing the intervention. This training will be conducted in a group and the use of the scales will be demonstrated and assessed to ensure that the implementers are familiar with both the content and use of the scales. In addition, testing and collection of questionnaire responses will be conducted on the spot to ensure the validity and recall of the questionnaire.

### Statistical analysis

2.8

For quantitative analysis, Epidata 3.1 (Epidata Association) will be used for double data entry and SPSS 26.0 (International Business Machines Corporation, IBM) will be used for data analysis and processing. Descriptive statistics will be used to describe participants’ characteristics and mental health outcomes. For continuous variables, the Shapiro–Wilk test (S-W test) will be used to assess normality. Depending on the results of the S-W test, the mean and standard deviation or the median and the interquartile range will be used for descriptive statistics. For categorical variables, frequencies and percentages will be reported. Independent samples t-tests, Mann–Whitney U tests and χ^2^ tests will be used to compare outcome results and baseline data. Paired sample t-tests or non-parametric rank sum tests will be used to compare the outcomes within the group. To analyze between-group differences, a two-independent sample t-test or a Mann–Whitney U rank sum test will be used. The changing trend of the outcome indicators of the study subjects will be measured between T_0_, T_1_, T_2_, and T_3_; the inter-group factor will be the subgroup (EIG and CG), the intra-group factor will be the measurement time point (T_0_, T_1_, T_2_, and T_3_), and the interaction will be the group × time point. A generalized linear mixed model will be used for analysis. The significance level of all the above statistical tests will be set at *p* ≤ 0.05, indicating a significant statistical difference.

Regarding qualitative data analysis, one researcher will transcribe the interview audio recordings within 24 h after the interview and enter the transcriptions into Nvivo 12 (QSR International Pty Ltd), and another researcher will checked these transcriptions. Nvivo 12 will be used for coding, and data will be analyzed and collected in parallel. Qualitative content analysis will be applied to the data collected (44, 45). This method is an objective, systematic and quantitative research method applied to text content, which is based on the generation of explicit and descriptive content categories and the generation implicit and explanatory content themes. First, researchers will read the transcripts multiple times to get a sense of the data as a whole. Secondly, a series of open codes will be identified, and similar and related codes will be classified into subcategories. These subcategories will be then abstracted into generic categories, and finally, general categories will be summarized into main categories. Two researchers will analyze the data at the same time and compare their coding frameworks. If there is a disagreement, a third researcher will be consulted until an agreement is reached to improve the quality of the analysis.

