**Methods:**

This study will employ an explanatory sequential design, starting with a quantitative evaluation using a randomized controlled trial (RCT), followed by a supplementary qualitative study. College students identified as having StD will be randomly allocated in a 1:1 ratio into the exergame intervention group (EIG) or the control group (CG). College students in the EIG will participate in a Nintendo Switch-based exergame program for 8 weeks, with 2–3 sessions per week, lasting 50–60 min each. Participant outcomes in both conditions will be assessed at pre-intervention (T_0_, week 0), post-intervention (T_1_, week 8), 1 month after the intervention (T_2_, week 12), and 2 months after the intervention (T_3_, week 16), and a generalized linear mixed model will be used for analysis. In the qualitative part of this study, interviews will be conducted with college students with StD from the EIG at T_1_ to explore their experiences of receiving the intervention, and content analysis will be applied to the data collected.

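### Section 2.8 tests the group difference by a simple two-sample test with no stated baseline adjustment and also by a group × time mixed model, without saying which decides

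*Protocol article*

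**What the plan says.** Section 2.8 (Statistical analysis) of the protocol article gives two routes to the group comparison.

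- **Simple tests.** "Independent samples t-tests, Mann–Whitney U tests and χ^2^ tests will be used to compare outcome results and baseline data", and again: "To analyze between-group differences, a two-independent sample t-test or a Mann–Whitney U rank sum test will be used". No baseline covariate is named, and the text does not say whether raw scores or changes from T0 are compared.
- **Longitudinal model.** Group is the between-subject factor and T0, T1, T2 and T3 are the levels of the within-subject factor, "and the interaction will be the group × time point". Then: "A generalized linear mixed model will be used for analysis".

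The section closes by applying p ≤ 0.05 to all the tests it lists. It does not say which analysis, or which time point, decides efficacy. The abstract (Methods) mentions only the second route: "a generalized linear mixed model will be used for analysis".

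On normality: "For continuous variables, the Shapiro–Wilk test (S-W test) will be used to assess normality". The only consequence written down is for description: depending on the result, "the mean and standard deviation or the median and the interquartile range will be used for descriptive statistics".

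The Introduction hypothesises improvement compared with control, maintained at the 2-month follow-up (T3).

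**The concern.** Two analyses address the same question at the same threshold, and they can disagree. With no rule for which one counts, the conclusion could be chosen after both p-values are known. The article itself creates this conflict, because it prescribes both analyses. A separate analysis plan would have to rank or override this text.

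As described, neither route is the most direct answer to the hypothesis. The simple test makes no stated use of the T0 score, although Table 2 shows T0 collected on every scale. The interaction asks whether the two four-visit profiles differ in any way. It does not by itself estimate the difference at T1 or at T3. At stake are control of the false-positive rate for the main claim and some power that would cost nothing to gain.

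**Working it through.** **Inputs from the article.** Standardised effect 0.69, power 80%, significance level 5%, attrition 10%, 38 per arm (section 2.2); 1:1 allocation (section 2.4); visits T0 to T3 (section 2.6.1).

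**Assumptions not in the article.** Two-sided testing; pre-post correlation r; equal correlation r between all visits (compound symmetry); effect sizes at T2 and T3.

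**1. The plan's own figure.** A two-sided, unadjusted two-sample t-test (noncentral t) with effect 0.69 and 80% power needs 33.96, so 34 per arm. Then 34 / 0.90 = 37.8, so 38 per arm and 76 in total. The stated figure reproduces, and it matches the simple-test route. Power with 34 evaluable per arm is 80.0%.

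**2. Baseline-adjusted T1 contrast.** Adjusting for T0 multiplies the residual variance by 1 − r², so the effective effect size is 0.69 / √(1 − r²). With 34 per arm:

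| r | effective effect | power | n per arm for 80% |
|---|---|---|---|
| no adjustment | 0.690 | 80.0% | 34 |
| 0.3 | 0.723 | 83.6% | 31 |
| 0.5 | 0.797 | 89.9% | 26 |
| 0.7 | 0.966 | 97.5% | 18 |

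If the t-test were meant for change scores, the effective effect would be 0.69 / √(2(1 − r)). Power is then 65.9%, 80.0% and 95.1% at r = 0.3, 0.5 and 0.7, below the adjusted contrast each time.

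**3. The 3-df interaction.** Let d₁, d₂, d₃ be the effects at T1 to T3, with none at T0. Under compound symmetry the noncentrality is λ = (n/2) · [Σd² − (Σd)²/4] / (1 − r), with 3 and 198 degrees of freedom.

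- Decaying effects 0.69/0.50/0.35: Σd² = 0.8486 and (1.54)²/4 = 0.5929, difference 0.2557. At r = 0.5, λ = 17 × 0.2557 / 0.5 = 8.69.
- Maintained 0.69: Σd² = 1.4283 and (2.07)²/4 = 1.0712, difference 0.3571. At r = 0.5, λ = 17 × 0.3571 / 0.5 = 12.14.

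| r | power, decaying | power, maintained |
|---|---|---|
| 0.4 | 60% | 76% |
| 0.5 | 68% | 84% |
| 0.6 | 79% | 91% |

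**4. False positives if either route may be claimed.** Null trials were simulated with 34 per arm, four visits and compound symmetry (8,000 runs per setting, Monte Carlo standard error about 0.3 points). The T1 test was a t-test or a Mann–Whitney test according to Shapiro–Wilk.

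- T1 test alone, normal data: 5.1–5.6%.
- Interaction alone, normal data: 5.0–5.1%.
- Either one: 9.5%, 9.6% and 9.6% at r = 0.3, 0.5 and 0.7; 9.3% with skewed data at r = 0.5.
- Reference for two independent tests: 1 − 0.95² = 9.75%.

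**The case against.** The strongest reply is that the simple tests are per-visit summaries and the mixed model is the real analysis, as the abstract suggests. On that reading no second route to a claim exists, and the 9–10% does not describe the plan. This stands in part: the article never says that either result may be claimed, so the figure is a worst case. It does not remove the ambiguity, because section 2.8 assigns between-group differences to the simple tests by name and gives them the same threshold.

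Several stronger readings are tempting, and the article does not support them:

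- **That the plan as a whole wastes baseline data.** The mixed model includes T0 as a level of time. The point applies only to the simple tests, and even there raw versus change scores is left open.
- **That Shapiro–Wilk selects the between-group test.** This is plausible, but the written link is to descriptive statistics only. In the simulation the gating itself added little error.
- **That the interaction is clearly weaker than the t-test.** This holds at r = 0.4 to 0.6 if effects decay. If 0.69 is maintained, which is closer to the article's hypothesis, the interaction has 84% power at r = 0.5 against 80%.
- **That maintenance cannot be tested.** A model with group, time and group × time can yield T1 and T3 differences. The article does not name them as the deciding contrasts, and an article may leave that detail to a fuller document.

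It is also fair that the unadjusted test is valid and that 76 participants already give it 80% power. Baseline adjustment is a gain in efficiency, not the repair of an invalid test.

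**Conclusion.** The point holds in limited form. Section 2.8 prescribes two between-group analyses of the same outcomes at the same threshold and ranks neither, while the abstract names one. The worst-case false-positive rate for one outcome is about 9–10%, conditional on either the T1 test or the interaction being accepted as success.

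At r = 0.3 to 0.7, a single baseline-adjusted T1 contrast would raise power from 80% to between about 84% and 98%, using data already collected. That gain rests on 34 evaluable per arm, an effect of 0.69 at T1 and the assumed correlation. The interaction's power is too dependent on the assumed profile and correlation (60–79% or 76–91% at r = 0.4 to 0.6) to support a general ranking against the t-test. The change should be made, but the design and sample size are not in question.

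**What to change.** Rewrite the between-group part of section 2.8 so that the mixed model is the single confirmatory analysis:

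- Outcomes at T1, T2 and T3, with T0 score, group, visit and group × visit as fixed effects. Equivalently, keep T0 as an outcome and constrain the two arms to a common baseline mean.
- The group difference at T1 as the primary contrast and the group difference at T3 as the maintenance contrast, each with a 95% CI.
- The t-test and Mann–Whitney comparisons of outcomes either dropped or labelled as sensitivity analyses. If they stay, state whether they use raw or change scores and what decides between them.

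The abstract already names the mixed model and needs no change. The cost is wording only: the visits, scales, software and total of 76 are unchanged.
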